## Assignment of interventions: blinding

### Who will be blinded {17a}

Due to the study design, which compares a drug therapy with an interventional procedure, neither the patients nor the physicians can be blinded. In addition, the embolizate used in the embolization of the patients treated in the control group will always be visible in the imaging control examinations in both MRI and CT, so that neither the radiologist nor the neurosurgeon can be meaningfully blinded here.

### Procedure for unblinding if needed {17b}

Not applicable as it is not a blinded study.

## Data collection and management

### Plans for assessment and collection of outcomes {18a} and data management {19}

Neurological examination results (NIHSS and mRS) at baseline and at each follow-up time point will be recorded and securely stored by the clinical investigators and supporting study personnel in the form of paper data sheets. The size and extent of the CSDH will be measured using CT or MRI scans without contrast. The volume is measured using a medical image viewing program. (Fig. 2) Follow-up is carried out as shown in Table 1 at 1 week, 1, 2, and 3 months postoperatively after relief of the CSDH during outpatient follow-up visits.

**Fig. 2 Fig2:**
[figure not shown]
Preoperative volume measurement of a right-sided hemispheric chronic subdural hematoma using the CT data set

The following intervention-associated complications will be documented as part of the study:Vascular dissections caused by the guidewireDislocation of embolized materialIschemia caused by vascular occlusion during the interventionInflammation or abscesses at the puncture siteVascular fistula in the area of the puncture siteRetinal blindnessEpidural hematomas after perforation of the meningeal arteryAllergic reactions to the contrast mediumAcute renal failure

The following complications or adverse events associated with the use of tranexamic acid will be documented:Intolerance reactionsPulmonary embolismsVenous thrombosisEpileptic seizuresMyocardial infarctionsCerebral ischemic infarctionsAcute renal failure

All research data, including baseline data (NIHSS, mRS, hematoma volume, patient demographics and characteristics) prior to surgery, will be collected anonymously in an electronic data collection form at each study center. The PI of the trial summarizes these for all centers and exports data for statistical analysis. All investigators will be trained to perform outcome measurements and will be introduced to the data management prior to recruitment of the first patient.

### Plans to promote participant retention and complete follow‐up {18b}

Participants will be informed about the study’s objective and relevance. The importance of completing the treatment and the follow-up evaluation, both for the study’s quality and for their personal chance to benefit from the therapy, will be emphasized. Participating patients are consciously informed that there are no personal benefits to take part in the study. Nevertheless, it is also explained that there is scientific evidence that patients who are treated as part of a clinical trial can obtain better results than patients who are treated under routine conditions.

Study follow-up is performed at 1 week and 1, 2, and 3 month (± 1 week) after evacuation of the hematoma with an outpatient clinic visit and CT or MRI scans. During these visits, all outcome measurements are performed by one of the researchers. To maximize participant retention, this study follow-up is parallel to the regular follow-up in the outpatient clinic (standard treatment). In addition, appointments for follow-up examinations are made as soon as the patient is discharged from inpatient treatment in order to increase compliance with participation.

### Confidentiality {27}

All persons involved in the study are bound to confidentiality. All data is collected and analyzed in pseudonymous form. Extensive measures are taken to protect the data, especially personal data, from access by third parties. Local therapy files and study data are kept in locked cabinets and are only accessible to the study staff and the respective treating therapists, who are subject to legal confidentiality.

All treatment cases are managed using identification codes or anonymized registration numbers. The semantics of the patient coding is specified by the Principal Investigator (PI) of the trial and consists of the study center number (two digits) and a consecutive number within the study center (three digits). The correspondence table of anonymization codes and names as well as the consent form with the names are kept strictly in a separate, lockable document storage and managed by the principal investigator of the respective center. The pseudonymous research data will only be shared after a data transfer agreement is signed. If participants withdraw their consent to the study, they will be asked about the reasons for their early withdrawal. The data collected to date will continue to be used and analyzed as part of the study unless the participants withdraw their consent to the processing of their data.

### Plans for collection, laboratory evaluation and storage of biological specimens for genetic or molecular analysis in this trial/future use {33}

Not applicable as no biological specimens are collected as part of this trial.

## Statistical methods

### Statistical methods for primary and secondary outcomes {20a}

The baseline data and outcome parameters are subjected to a simple descriptive data analysis (median, minimum, maximum and standard deviation in each case; mean only for metrically scaled characteristics).

For difference tests for nominal variables (gender, use of anticoagulation prior to surgery, occurrence of complications due to adjuvant therapy procedures, need for revision surgery), the Pearson chi-squared test is used.

For difference tests of ordinally scaled measured variables (NIHSS, mRS) within the respective groups at different points in time (linked samples), the data collected is tested for normal distribution using the Shapiro–Wilk test. In the case of a parametric distribution, the *t*-test is used for linked samples. In the case of a non-parametric distribution, the Wilcoxon test is used for connected samples (for two-group tests).

For the bivariate dependency analysis of the ordinal scaled characteristics between the two groups at the same point in time, the *t*-test for unconnected samples is used for a parametric distribution and the Mann–Whitney *U*-test for a non-parametric distribution after applying the Shapiro–Wilk test.

For metric variables (hematoma volume), which are subject to a normal distribution, the *t*-test for dependent samples is used to analyze the respective groups at different points in time. In the case of a non-parametric distribution, the Wilcox sign-rank test is used for the analysis.

For the bivariate dependency analysis of the metric characteristics between the two groups at the same point in time, after applying the Shapiro–Wilk test, the *t*-test for unrelated samples is used for a parametric distribution and the Mann–Whitney *U*-test for a non-parametric distribution.

In addition, a logistic regression is tested with the revision rate as the dependent variable and the treatment groups and baseline data as independent variables.

Furthermore, a correlation analysis of the relationship between the postoperative volume size and the revision rate as well as the postoperative neurological assessment and the revision rate is performed, in each case for mixed scaling pairs with the chi-squared test. The respective singular correlation analysis is followed by an analysis of the existence of a partial correlation between the two parameters in relation to the revision rate.

The significance level is set at *p* < 0.05 in each case.

The statistical analysis is performed with SPSS.

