In addition, complications in relation to the interventional procedure and complications and side effects due to the use of tranexamic acid will be documented.

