## Assignment of interventions: allocation

### Sequence generation {16a}, concealment mechanism {16b}, and implementation {16c}

After the neurosurgeon has checked the inclusion and exclusion criteria, the participants are assigned to treatment with tranexamic acid or embolization in a 1:1 ratio in each study center by means of block randomization after they have given their informed consent and the baseline data have been recorded.

If, in the course of the randomized group allocation, it will be apparent that there are exclusion criteria for inclusion in the test group in the sense of contraindications for the administration of tranexamic acid, or if it will be determine during the procedure that vascular anomalies prevent embolization in patients randomized to the control group, a crossover to the corresponding comparison group is possible after prior further clarification.

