### Adverse event reporting and harms {22}

Adverse events are defined as any undesirable experience occurring to a subject during the study, whether or not considered related to the investigational product (TXA) or investigational intervention (embolization). After participants have provided consent and been enrolled in the study, adverse events or complications of the treatment, will be documented and recorded until the end of the study period. Any serious adverse event that occurs in this trial will be reported to the principal investigator (PI). The PI must decide whether the participant can continue to participate in the study or whether he or she has to be excluded. The study team in every participating center will take responsibility for the treatment of the trails related adverse events or complications. The PI of the study will consider the continuation or discontinuation of the research under the following circumstances:◦ If a serious adverse event or disease report suggests that continuing the study poses safety concerns◦ If recruiting participants for the study becomes challenging, making it difficult to achieve the planned number of cases◦ When significant new information regarding the quality, safety, or efficacy of the medication (TXA) and interventional procedure (embolization) is obtained

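### The planned chi-squared test of complications uses treatment-attributed events from two non-matching lists; it should use one common list and all serious adverse events by randomized arm

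*Protocol article*

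**What the plan says.** Complications are a tertiary outcome. The section on the tertiary outcome defines them by treatment: "complications in relation to the interventional procedure and complications and side effects due to the use of tranexamic acid will be documented". The tertiary objectives make the same split.

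The section on assessment and collection of outcomes {18a} gives two lists. The first is introduced with "The following intervention-associated complications will be documented as part of the study" and has nine items. The second is introduced with "The following complications or adverse events associated with the use of tranexamic acid will be documented" and has seven items.

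Section {20a} names "occurrence of complications due to adjuvant therapy procedures" among the nominal variables for difference tests, for which "the Pearson chi-squared test is used" at the 0.05 level.

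The section on adverse event reporting {22} is wider: "Adverse events are defined as any undesirable experience occurring to a subject during the study, whether or not considered related" to either treatment. No comparison between arms is attached to that record.

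Section {17a} says that neither patients nor physicians can be blinded. The allocation section adds that, where the assigned treatment proves unsuitable, "a crossover to the corresponding comparison group is possible after prior further clarification".

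**The concern.** A between-arm test of a yes/no safety outcome needs the same definition in both arms. Here the variable is what each treatment is held to have caused, and the two sets of candidate events differ. A pulmonary embolism or seizure in the second month is a listed complication for a TXA patient and has no place on the embolization list. Yet the background section itself names epileptic seizures as a symptom of the hematoma, so they can occur in either arm. Whether an event is due to treatment would be judged by people who know which treatment was given.

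The abstract names the complication rate as a tertiary endpoint, and the discussion presents the trial as a way to weigh the risk-benefit ratio of the two treatments. A p-value from this test would be read as evidence on that question, although part of any difference could come from the counting rule.

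**Working it through.** **1. The two lists in {18a}, side by side**

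| Event | Embolization list | TXA list |
|---|---|---|
| Pulmonary embolism | no | yes |
| Venous thrombosis | no | yes |
| Epileptic seizure | no | yes |
| Myocardial infarction | no | yes |
| Cerebral ischemia | only from occlusion during the procedure | yes, unrestricted |
| Hypersensitivity | contrast allergy only | intolerance reactions |
| Acute renal failure | yes | yes |
| Dissection, displaced embolic material, puncture-site infection or fistula, retinal blindness, epidural hematoma | yes | no |

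Four of the seven TXA items have no counterpart, two overlap in part and one is identical.

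**2. The plan's own figure.** The sample size section assumes recurrence of 10% (embolization) and 2% (TXA), α = 0.05 and power above 0.8. Two-sided, with pooled variance under the null:

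n = [1.960·√(2·0.06·0.94) + 0.8416·√(0.10·0.90 + 0.02·0.98)]² / 0.08² = 137.2, so 138 per group and 276 in total.

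The stated size reproduces and is not in dispute. I use 138 per arm below.

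**3. How few events suffice.** For k events v 0 in equal arms, the uncorrected Pearson statistic is 276·k/(276 − k).

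- k = 3: 276·3/273 = 3.03, p = 0.082.
- k = 4: 276·4/272 = 4.06, p = 0.044.

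**4. Equal true rates, unequal counting.** The documents give no complication rates, so every rate from here on is an assumption. Let events found only on the TXA list occur at the same true rate r in both arms but count only under TXA. If nothing else is counted, the test rejects when X ≥ 4, with X ~ Binomial(138, r). The last two columns add a further 5% of patients per arm with some other counted complication, or use one common list. Both come from summing exact binomial probabilities over all outcomes where the statistic exceeds 3.84.

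| r | Expected TXA count (138·r) | Reject, nothing else counted | Reject, 5% other complications per arm | Reject, one common list |
|---|---|---|---|---|
| 1% | 1.4 | 0.05 | 0.06 | 0.03 to 0.05 |
| 2% | 2.8 | 0.30 | 0.10 | 0.05 |
| 3% | 4.1 | 0.60 | 0.16 | 0.04 to 0.05 |
| 5% | 6.9 | 0.92 | 0.33 | 0.05 |

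**5. Embolization has procedural events of its own.** Let background events at rate r occur in both arms but count only under TXA, and let procedural events at rate q occur and count only under embolization. The counted rates are then r v q, while the embolization any-cause rate is 1 − (1 − r)(1 − q).

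| Counted, TXA v embolization | Any-cause, TXA v embolization | Chance of p < 0.05 on counted events |
|---|---|---|
| 5% v 2% | 5% v 6.9% | 25%, nearly all against TXA |
| 3% v 2% | 3% v 4.9% | 7%, mostly against TXA |
| 3% v 5% | 3% v 7.9% | 12%, favouring TXA |

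In the first two rows the test leans against the arm with the lower any-cause rate. In the third row it leans the right way but is weakened: on a common list, 3% v 7.9% would be significant in about 43% of trials.

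**The case against.** The strongest reply is that the article does not fix what the concern needs. It does not say that each list is applied only in its own arm, or that the lists are merged into one yes/no variable. The variable stands in a parenthesis and could be meant item by item. Form layout and coding usually belong to the full protocol or the analysis plan, which are not shown. This stands in part. The arm-specific use is an inference, drawn from the list headings, the split definition of the tertiary outcome and the causal wording of the tested variable. It is still the natural reading, and the article itself chose that variable and that test.

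A reader might infer that every event counts in one arm and not in the other. The lists do not support that: renal failure is on both, and ischemia and hypersensitivity overlap in part. Purely procedural items can occur only with the procedure and are properly counted there as treatment burden.

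A reader might also infer that safety data will be lost. They will not, because the adverse event section records events regardless of relation.

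Finally, the larger probabilities assume that every background event is attributed to TXA and that embolization has few or no counted events. An event judged unrelated would drop out. Patients with TXA contraindications, including past seizures or thrombosis, may also cross over to embolization, so equal background rates by treatment received are not assured. These points stand, and they are why a range is given.

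**Conclusion.** The concern holds in a limited form. As its headings read, the plan tests treatment-attributed complications under definitions that do not match for pulmonary embolism, venous thrombosis, seizures and myocardial infarction, and match only in part for cerebral ischemia and hypersensitivity. Attribution is unblinded.

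The size is not determined by the documents. Under the assumptions stated above, the chance of a significant result due to the counting rule alone runs from about 5% (1% TXA-list-only events, nothing else counted) to 92% (5%, nothing else counted). It is about 25% for counted rates of 5% v 2% and 7% for 3% v 2%. It would be wrong to conclude that the test will almost surely show a false difference, or that the bias always runs against TXA: at 3% v 5% the significant results favour TXA.

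The defect lies in the tested variable, not in data capture. It concerns a tertiary outcome and leaves the primary analysis and the sample size untouched. It should be corrected, but it does not threaten the trial.

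**What to change.** In {20a}, replace the complication variable in the chi-squared test with two outcomes, each compared by randomized arm with a risk difference and 95% confidence interval:

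- any event from one combined list (the union of the two lists in {18a}), recorded in both arms from randomization to 3 months;
- any serious adverse event over the same period.

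Count both regardless of presumed cause, drawing on the adverse event record in {22}. Naming the randomized arm also settles where the events of crossed-over patients are counted. Report treatment-attributed and procedure-specific complications in descriptive tables only, without a between-arm test.

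The cost is one shared case report form page and one analysis sentence, made by amendment because recruitment has begun. For patients already enrolled, the adverse event record should already hold the events. No clinical rule changes.

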### Criteria for discontinuing or modifying allocated interventions {11b}

Patients may withdraw their consent at any time without providing a reason and thus terminate their participation in the study prematurely. Withdrawal from the study and reasons, if known, will be documented. Study treatment stops if a surgical treatment for the CSDH is necessary during follow-up, in case of subsequent occurrence of an exclusion criterion or in occurrence of treatment-related complications during treatment. Crossover to the other study arm is not possible after the start of treatment in the respective study arm. Moreover, the principal investigator is entitled to terminate the study prematurely if new scientific findings in favor of one or the other treatment violate the equipoise principle.

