#### Secondary outcome

To answer the question specified in the secondary objective, the need for revision surgery on the primary side of patients included in the study is documented depending on the study arm as well as the time interval to the primary procedure.

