### Sample size {14}

In order to estimate the required sample size, the volume change of a primary operated CSDH under the adjuvant therapy forms to be investigated is analogized with the recurrence rates of primary operated and adjuvant embolized or adjuvant drug-treated CSDH in the literature with regard to the target value defined within the primary objective. For example, the MEMBRANE study, which is currently being recruited, assumes a recurrence rate of 10% when combined surgical and interventional therapy is used [11]. In comparison, the work of Hibahashi et al. [27] puts the recurrence rate of CSDH treated with a combination of surgery and medication at around 2%. Based on this, using the *z*-test for independent samples and an error of the first kind (*α* = 0.05), a sample size of 276 patients (138 per group) is required to achieve a power > 0.8 to detect a difference of 8%.

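### Revision surgery over 3 months is analysed only as yes/no, although patients can leave early and the recorded time to revision is used in no analysis

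*Protocol article*

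**What the plan says.** **Analysis.** Protocol article, Statistical methods {20a}, lists revision among the nominal variables: "need for revision surgery), the Pearson chi-squared test is used". The same section adds a logistic regression with revision as the dependent variable. Both are binary analyses.

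**What is recorded.** Under Secondary outcome, the need for revision "is documented depending on the study arm as well as the time interval to the primary procedure". Neither {20a} nor any other section names a method that uses this interval.

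**Early exit.** Section {11b} states: "Patients may withdraw their consent at any time without providing a reason and thus terminate their participation in the study prematurely". Under Adverse event reporting {22}, the principal investigator decides after a serious adverse event whether the participant continues or is excluded. For those who withdraw, Confidentiality {27} says: "The data collected to date will continue to be used and analyzed as part of the study", unless consent to data processing is also withdrawn.

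**Missing data.** Section {20c} plans exploratory analyses if a substantial share of the data is missing. It considers multiple imputation for covariates only.

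**Sample size.** Section {14}: "a sample size of 276 patients (138 per group) is required to achieve a power > 0.8 to detect a difference of 8" per cent. The inputs are recurrence rates of 10% with embolization and about 2% with tranexamic acid.

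**The concern.** A yes/no comparison at 3 months needs a known 3-month status for each patient. Someone who withdraws at week 1 without revision has a recorded status of no revision, but only for one week. The 2×2 table has no place for that difference. Two options remain: enter the patient as revision-free, which credits unobserved time as success, or drop the patient, which discards observed time and leaves a selected group. Death before revision raises the same choice, and scoring it as revision-free counts a death as a good result.

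Counting leavers as revision-free understates the rate most in the arm that loses more patients. The arms differ in ways that could make loss unequal: one is 3 months of daily medication, the other a single procedure, and exclusion after a serious adverse event is a judgement made in an unblinded trial. With few revisions expected, a handful of such patients could move the result, and their scoring is not fixed in advance.

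**Working it through.** **Inputs.** From Sample size {14}: 10% (embolization), 2% (tranexamic acid), alpha 0.05, 138 per arm. Sidedness is not stated; two-sided reproduces the plan's figure. Section {14} derives the number by analogy for the volume objective, but its inputs are recurrence rates, so using it for revision is fair. Attrition rates are assumptions, because the documents give none.

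**1. The plan's own figure.** Pooled two-proportion z-test, mean rate 0.06:

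n = [1.96·√(2·0.06·0.94) + 0.8416·√(0.10·0.90 + 0.02·0.98)]² / 0.08² = (0.658 + 0.279)² / 0.0064 ≈ 137.2, so 138 per arm.

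The stated 276 is reproduced. It is the formula minimum, with no allowance for loss. Expected revisions: 138 × 0.10 ≈ 14 and 138 × 0.02 ≈ 3.

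**2. Leavers counted as revision-free.** If a fraction L leaves and a fraction m of their revisions goes unseen, the observed rate is p·(1 − L·m).

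| Assumed loss (embolization v tranexamic acid) | m | Observed rates | Difference |
|---|---|---|---|
| none | – | 10.0% v 2.0% | 8.0 points |
| 15% v 5% | 1 | 8.5% v 1.9% | 6.6 points |
| 15% v 5% | 5/6 | 8.75% v 1.92% | 6.8 points |
| 15% v 5% | 1/2 | 9.25% v 1.95% | 7.3 points |
| 5% v 15% | 1 | 9.5% v 1.7% | 7.8 points |

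The value 5/6 applies if revisions are spread evenly over 3 months and leavers go, on average, after half a month. Simulating that case at 15% v 5% gave 6.8 points for the plain proportion. The cumulative incidence with leavers censored gave 8.0, which is the true difference. The simulation had no deaths, and leaving was unrelated to revision.

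If both true rates are 10%, loss of 15% v 5% with m = 1 gives 8.5% v 9.5%, a false 1-point difference. The exact rejection rate then moves from 0.051 to 0.061.

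**3. How few patients decide the test.** Uncorrected Pearson chi-squared, 138 per arm:

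- 10 v 3: 276·(10·135 − 128·3)² / (138·138·13·263) = 3.96, p = 0.047.
- 9 v 3: 276·(9·135 − 129·3)² / (138·138·12·264) = 3.14, p = 0.077.

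**4. Power if leavers are dropped.** The exact column enumerates both binomials for the Pearson test.

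| Scored per arm | Pooled formula | Exact Pearson |
|---|---|---|
| 138 | 0.802 | 0.839 |
| 137 | 0.7996 | 0.837 |
| 131 (5% loss) | 0.78 | 0.82 |
| 126 | 0.766 | 0.802 |
| 125 | 0.762 | 0.798 |
| 124 (10% loss) | 0.76 | 0.79 |

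**The case against.** **Convention and scope.** Chi-squared on a fixed 3-month outcome is a conventional choice and matches the z-test used for sizing. The article condenses a longer protocol, and scoring of death or early exit is often settled there or in an analysis plan. This stands in part: the absence of a scoring rule is not in itself the fault. But {20a} positively names the analysis, and that analysis leaves a recorded variable unused.

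**Missing-data section.** Section {20c} covers other analyses as well as the primary one, so it does reach revision. That is right, but it is triggered only by a substantial amount of missing data and sets no rule for the outcome.

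**Inference about leavers.** A reader might infer that the protocol itself scores leavers as revision-free. It does not. Confidentiality {27} says only that collected data remain usable, and dropping leavers is equally open. Nor do the documents give a mortality figure; they say only that incidence rises with age.

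**Power.** A reader might also infer that the stated power fails as soon as one patient per arm is unscored, or holds only if all 276 are scored. The pooled formula does give 0.7996 at 137 per arm, but that is a rounding edge. Exact power of the planned test is 0.837 there and stays above 0.80 down to 126 per arm, a loss of about 9%.

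**Limits of the alternative.** Time-to-event analysis does not recover unseen revisions, and a p-value near 0.05 would be fragile under any method. Both are true. Censoring removes the bias only if leaving is unrelated to impending revision.

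**Conclusion.** The point holds as an analysis choice that can be improved at little cost. Revision is fixed as a yes/no variable, early exit is foreseen, and the recorded time to revision is not used. If loss differs between arms and leavers enter as revision-free, the difference is biased. Under the assumed 15% v 5% early loss it falls from 8 to about 6.6 to 6.8 points. With later loss (m = 1/2) it is 7.3, and with the loss reversed it is 7.8. The effect on false-positive error is small (0.051 to 0.061). These sizes rest on assumed attrition and on a scoring choice that the protocol leaves open.

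The power statement should not be called wrong on this ground. At most, 138 per arm contains no allowance for loss. At an assumed 5% to 10% loss with leavers dropped, power is 0.78 to 0.76 by the pooled formula and 0.82 to 0.79 exactly.

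**What to change.** In {20a}, make time to first revision, by randomized arm, the main analysis of revision surgery, using the interval already recorded under Secondary outcome:

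- Estimate the 3-month cumulative incidence per arm, with death as a competing event.
- Censor withdrawals and losses at last contact.
- Report the between-arm difference with a 95% confidence interval.
- Keep the Pearson chi-squared test as a supporting analysis.
- Add a sensitivity analysis that counts revision or death as failure.

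Optionally, note in {14} that 138 per arm includes no allowance for loss, and give the power at an assumed loss by a named method.

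The cost is a wording change, recording the date of death or last contact, a presentation slightly less simple than a 2×2 table, and possibly software beyond the basic SPSS menus. No extra patients, visits or procedures are needed.
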